### Quality control and quality assurance

Outcome measurements will be collected by an experienced physiatrist, and physiotherapists in charge of the intervention will receive standardized training and assessments in advance. Before enrolment, an individual researcher will provide detailed information to the participants and their guardians to ensure that they understand the possible benefits of the treatment, thereby improving compliance.

A three-grade quality control system will be used for quality control: self-examinations from researchers, monthly examinations from group inspectors, and quarterly supervision from the research leader.

A clinical research unit (CRU) will be established to ensure the safety and validity of the data of this study. The CRU can terminate the trial early if a large number of adverse events occur or the data are proven to be invalid.

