#### Safety

Before the start of treatment, we will record the children’s history of seizures, syncope, headache, cognitive deficits, and behavioural disorders in detail. For children with adequate cognitive ability, subjective evaluation of treatment tolerance will be used to evaluate safety during and after treatment on a scale of 1 to 10, where 1 is the least pleasant and 10 is the most pleasant. If the score is less than 5 points, this reflects poor treatment tolerance, and the treatment will be stopped. For children with cognitive deficits, physiotherapists will observe the child’s expression during each treatment. According to the FPS-R, treatment should stop when there is frowning or deepening of the nasolabial groove on children’s faces. If mild adverse events occur (fatigue, local discomfort, headache), the treatment will be paused, the event will be recorded, and the treatment intensity will be adjusted. If severe adverse events (e.g., seizure) occur, the treatment will be stopped, emergency treatment will be provided, and the condition will be reported to the research leader.

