#### Secondary analysis

Data will be divided into an intention-to-treat analysis set and a safety analysis set. The intention-to-treat set will include subjects who were randomly assigned to groups and completed the baseline measurement. Subjects who received at least one intervention and underwent one safety assessment will be allocated to the safety analysis set. The change in secondary outcomes from before to after the intervention will be compared to determine the therapeutic effects in three groups using the intention-to-treat set through the same analytical method as the main analysis. The safety analysis will include counting the number of adverse events and the number of patients who drop out because of unbearable adverse events.

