Few adverse events have been reported in studies of rTMS utilizing high-frequency stimulation or low-frequency inhibition regimens. When rTMS is administered, the risk of seizures in children is very low (approximately 0.1%) [56]. Scalp discomfort at the irritation site and headache are mild and transient side effects of rTMS that may be reported by children and considered in the safety assessment in this protocol. VR therapy is considered a safe therapy, as a former meta-analysis showed that cybersickness and nausea are the most common side effects of VR therapy, with very low-certainty evidence, and no severe adverse events have been reported [17]. The treatment will be paused if cybersickness or nausea occur during the VR intervention.

This study protocol has some limitations. First, it may be difficult to blind the intervention practitioners (physiotherapists) during the intervention process because it may be easy for the physiotherapist to observe intervention methods in the immersive VR environment. Second, there may be bias in pain evaluations using the FLACC because of lower limb spasms in children with CP. To avoid the impact of lower limb spasms on the accuracy of pain assessment, pain assessment will be conducted by an experienced physiotherapist.

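### The safety set leaves out treated children who lack a safety assessment, one child can enter the event count repeatedly, and the trial-stop wording is not tied to severe-event reports

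*Protocol article*

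**What the plan says.** **Who is analysed for safety.** The Secondary analysis section of the protocol article sets two conditions: "Subjects who received at least one intervention and underwent one safety assessment will be allocated to the safety analysis set".

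**What is analysed.** The same section continues: "The safety analysis will include counting the number of adverse events and the number of patients who drop out because of unbearable adverse events".

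**What happens to the individual child.** The Safety section separates two grades of event. Mild events, with fatigue, local discomfort and headache as examples, lead to a pause, a record and an adjustment. For severe events, with seizure as the example, treatment stops, "emergency treatment will be provided, and the condition will be reported to the research leader". No other recipient is named.

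**What happens to the trial.** Under Quality control and quality assurance, "A clinical research unit (CRU) will be established to ensure the safety and validity of the data of this study", and then: "The CRU can terminate the trial early if a large number of adverse events occur or the data are proven to be invalid".

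**The concern.** Three stated rules weaken the harm assessment in a trial whose aim includes safety.

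- **Membership of the safety set depends on something that happens after treatment starts.** The child most likely to lack an assessment is one whose first visit is cut short. Excluding that child would remove the kind of case the set exists to capture, and the loss need not be equal across arms.
- **A count of events does not show how many children were affected.** One child with a recurrent mild complaint and many children with one complaint each can give the same total.
- **The trial-level criterion drops the article's own severity distinction.** It is worded by number alone. The one stated route for a severe event ends with the research leader, while the power to terminate is described for the CRU, and no sentence joins the two.

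**Working it through.** The article gives no numerical stopping threshold, so there is no stated figure to reproduce. The check compares the rules with each other and then asks how the count-based wording would respond to the severe event that the article names.

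**Inputs**
- Treatment days per child (Intervention): 2 blocks × 4 weeks × 3 days = 24.
- Children on active rTMS (two of three groups): 2 × 36 = 72 from the total of 108 under Ethics, or 2 × 49 = 98 from the total of 147 under Sample size. The two totals conflict, which is a separate matter, so both are carried.
- Seizure risk with rTMS in children (Discussion): about 0.1%. The article does not say whether this is per child or per stimulation, so both readings are shown. The second is an assumption.

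**1. The safety set.** The article does not define what counts as a safety assessment. There are two readings.
- Strict: a tolerance rating or an observation made during or after treatment must be completed. A child whose first visit ends before that is treated but excluded. Each omitted child who had an event removes 1/36 = 2.8 percentage points (or 1/49 = 2.0) from that arm's proportion, taken over all children randomised to the arm.
- Broad: any observation by the treating physiotherapist counts. Almost nobody is then excluded, and the second condition does no work.

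Under the strict reading the condition can bias the result. Under the broad reading it is redundant. Neither gives a reason to keep it.

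**2. The event count.** Suppose an arm has 24 recorded headaches.
- All from one child on 24 days: children affected = 1/36 = 2.8% (1/49 = 2.0%).
- One each from 24 children: children affected = 24/36 = 66.7% (24/49 = 49.0%).

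The event total is 24 in both cases. The 24-day child is an upper bound, because a mild event leads to a pause and an adjustment.

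**3. The stop criterion and the named severe event.**

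Per-child reading, with X ~ Binomial(n, 0.001) and P(X ≥ 2) = 1 − 0.999ⁿ − n × 0.001 × 0.999ⁿ⁻¹:

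| | n = 72 | n = 98 |
|---|---|---|
| Expected seizures, n × 0.001 | 0.07 | 0.10 |
| P(at least 1) | 7.0% | 9.3% |
| P(at least 2) | 0.24% | 0.45% |

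Per-treatment-day reading (assumption), with m = 24n:

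| | m = 72 × 24 = 1,728 | m = 98 × 24 = 2,352 |
|---|---|---|
| Expected seizures, m × 0.001 | 1.7 | 2.4 |
| P(at least 2) | 52% | 68% |

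On either reading seizures would number from none to a handful. Mild events can accrue over the same 1,728 to 2,352 treatment days. A criterion worded by number alone therefore responds weakly to the severe event that the article itself names.

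**The case against.** **This is a condensed article.** Reporting routes to the CRU and its working procedures commonly sit in the full protocol, and detailed safety tables in the analysis plan. That stands: a missing route is not an error in itself. What remains are rules the article does state, namely the two-part definition of the safety set, the named event count, and a termination criterion without severity.

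**A stopped first visit probably includes an assessment.** The Safety section covers evaluation during and after treatment, and observation at each treatment for children with cognitive deficits. That is fair, and no actual exclusion is shown. The wording still permits one.

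**A reader might infer that a severe event cannot lead the CRU to act.** The text does not support this. A seizure is an adverse event and enters the count, the meaning of a large number is left to judgement, the CRU is given a safety remit, and nothing bars the research leader from passing a report on. The leader's quarterly supervision is routine quality control and does not show that an event-driven report would be delayed.

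**A reader might infer that the safety analysis is only a raw count.** It is not. Dropouts for intolerable events are counted per patient, so repeat reporters cannot inflate that figure, and the article's list of safety analyses is not worded as exhaustive.

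**A reader might infer that the VR + rTMS arm will accrue more fatigue** because its visits last 60 + 40 + 20 = 120 minutes against 60 + 20 = 80. The documents give no figure for this. If it happened, it would be a genuine burden that a safety comparison ought to show.

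**Conclusion.** The point holds in a limited form. The safety-set definition can leave out a treated child, and the named event count lets one child contribute on up to 24 days. Both are weaknesses of stated text that can be corrected at almost no cost. How many children would be affected cannot be derived from the article; one omitted child with an event is worth 2.0 to 2.8 percentage points in an arm.

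On termination, the finding is that the Safety section and the Quality control section do not connect and that severity is absent from the criterion. The seizure figures rest on the article's 0.1%, on independence between children or treatment days, and, for the expected 1.7 to 2.4 events, on the assumed per-treatment-day reading. They show that a count responds weakly to this event, not that the CRU would fail to act.

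Safety is a stated aim of the trial. It should not be read as a co-primary outcome: the single primary outcome is the R-FLACC score.

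**What to change.** 1. Define the safety set as all children who received any intervention, with no condition on a later assessment.
2. Keep the event count and the dropout count, and add for each arm the number and proportion of children with at least one event, by severity.
3. Reconcile the Safety section with Quality control and quality assurance so that severe-event reports visibly reach the body able to terminate the trial, and so that the termination wording is consistent with the mild and severe grades already in use. The criterion itself is for the sponsor and investigators to set; no threshold is proposed here.

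The cost is a few sentences and one table. The Safety section already distinguishes mild from severe events and provides for recording them, so no new measurement should be needed and the sample size is unaffected.

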## Discussion

This protocol aims to explore the safety and effects of VR therapy combined with rTMS on pain and motor development in children with spastic CP. Considering comfort and the possibility of visual impairment in children with CP, we chose immersive VR training in this protocol, which is easier for physiotherapists to use than VR glasses or gamepads [49]. Kirton et al. [50] applied 1 Hz rTMS at 100% rMT for 20 min over the contralesional M1 for 8 days in children with hemiplegia. We chose a similar rTMS program since it resulted in significant motor improvement and was demonstrated to be safe and well tolerated.

The results of this protocol may reveal the additive effects of the combination of VR therapy and rTMS or the effects of rTMS only on pain management in spastic CP patients. Self-reported pain or observation of pain-related behaviours are the two main methods for pain assessment in spastic CP patients due to their potential impairments in cognition and verbal expression. Self-reported pain assessments are strongly recommended by guidelines for measuring the severity of pain, but it may not be reliable if the participants have cognitive deficits [51]. Tools for pain assessment, such as the FLACC, are widely used in individuals with cognitive or intellectual impairment [52]. The design of the FLACC was based on 89 postoperative children in the post-anaesthesia care unit aged 2 months to 7 years, and it was developed to evaluate pain in children who cannot express pain in words [53]. A previous study showed that the FLACC pain score was valid (Pearson’s correlation coefficients of 0.76 and 0.59 with the observational visual analogue scale score) and reliable (Cronbach’s alpha > 0.9) for assessing pain in children with CP; however, this study demonstrated insufficient validity in adult patients [54, 55].

In addition to the assessment of pain and motor development, we plan to utilize balance, activity of daily living, and quality of life assessments, which may reflect the possibility of these children to return to family and school. This study protocol may further bridge the gaps among pain, motor development, and functional independence, and the results may reveal the impact of pain on returning to society in children with CP.

Few adverse events have been reported in studies of rTMS utilizing high-frequency stimulation or low-frequency inhibition regimens. When rTMS is administered, the risk of seizures in children is very low (approximately 0.1%) [56]. Scalp discomfort at the irritation site and headache are mild and transient side effects of rTMS that may be reported by children and considered in the safety assessment in this protocol. VR therapy is considered a safe therapy, as a former meta-analysis showed that cybersickness and nausea are the most common side effects of VR therapy, with very low-certainty evidence, and no severe adverse events have been reported [17]. The treatment will be paused if cybersickness or nausea occur during the VR intervention.

This study protocol has some limitations. First, it may be difficult to blind the intervention practitioners (physiotherapists) during the intervention process because it may be easy for the physiotherapist to observe intervention methods in the immersive VR environment. Second, there may be bias in pain evaluations using the FLACC because of lower limb spasms in children with CP. To avoid the impact of lower limb spasms on the accuracy of pain assessment, pain assessment will be conducted by an experienced physiotherapist.

## Clinical implications

We expect to identify an effective method for simultaneously relieving pain in children with spastic CP and promoting motor function. Effective pain management can improve the quality of life of CP patients and is key to achieving better psychological development and overall prognosis. The results of this study may support future clinical practice and provide high-quality evidence regarding new approaches for pain management for children with CP. In addition, since central nervous system disorders frequently involve both pain and motor dysfunction [57], future studies should focus on the potential of combining VR therapy and rTMS in pain management in adults with neuropathic or musculoskeletal pain.

## Data Availability

Not applicable.

## Abbreviations

CP: Cerebral palsy
VR: Virtual reality
rTMS: Repetitive transcranial magnetic stimulation
GMFCS: Gross Motor Function Classification System
M1: Primary motor cortex
R-FLACC: Revised Face, Legs, Activity, Cry, and Consolability Scale
GMFM-66: 66-item version of the Gross Motor Function Measure
FMFM: Fine Motor Function Measure
C-CPQOL-Child: Chinese version of the Cerebral Palsy Quality of Life Scale for children
PedsQL-CP: Pediatric Quality of Life Inventory Measurement Model:Cerebral Palsy Module
rMT: Resting motor threshold
